## Outcomes

### Primary outcome

Gastrointestinal Quality of Life Index (GIQLI) - difference between 0 months and 6 months from randomisation.

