### Secondary variables

1. Gastrointestinal Quality of Life Index (GIQLI) at 12 months, 24 months, 48 months and 96 months of randomisation.
2. SF-36 quality of life survey score at 6 months, 12 months, 24 months, 48 months and 96 months from randomisation.
3. Recurrence of diverticulitis and Hinchey class.
4. Undergoing emergency surgery due to diverticulosis / diverticulitis.
5. Undergoing elective sigmoid resection (conservative treatment group).
6. Complications of elective sigmoid resection.
7. Mortality (for any reason in both groups).
8. Complications of diverticulosis (fistula, stricture).
9. Stoma (permanent / temporary).

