## The sample size

In previous publications, preoperative GIQLI has been 95-100 (SD 22) and postoperative GIQLI 112-114 (SD 19-22) (Forgione et al., 2009; Pasternak et al., 2011). The sample size calculation was made using these values, and the study aims to show a difference of 12 GIQLI points, the standard deviation being assumed to be 22 points in both groups. Using 0.05 alpha, 0.9 power, and 1: 1 allocation, a sample size per group of 60 patients is obtained. The sample size calculation was performed using G \* Power 3.1.5.1 (comparison of means, two-tailed, A priori). Approximately 10% of patients are estimated to disappear at follow-up, bringing the final sample size to a total of 133 patients.

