## Statistical analysis plan (amendment 5th Aug 2020)

Primary outcome and continuous secondary outcomes that are normally distributed will be compared using t-test and effect size will be reported as mean difference with 95% confidence interval (95%CI). Continuous secondary outcomes that were not normally distributed will be compared using Mann-Whitney U test and effect size will be reported as  $r (=Z/\sqrt{N})$  without 95%CI. Categorical secondary outcomes will be compared

using Fischer's exact test (if expected cases in one cell <5) or  $\chi^2$  test and effect size will be reported as odds ratios (OR) with 95% CIs. All outcomes will be analyzed using intention-to-treat principle where patients are analyzed in the group where they were randomized to.

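### Continuous secondary outcomes judged non-normal are to be reported only as r = Z/√N without a confidence interval, so later GIQLI and any SF-36 results may have no estimate in scale points and no stated precision

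*Supplement*

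**What the plan says.** In the latest protocol in the Supplement, the section Statistical analysis plan (amendment 5th Aug 2020) sets two rules for continuous outcomes.

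- The primary outcome and normally distributed secondary outcomes are "compared using t-test and effect size will be reported as mean difference with 95% confidence interval (95%CI").
- For the others: "Continuous secondary outcomes that were not normally distributed will be compared using Mann-Whitney U test and effect size will be reported as" r, defined as Z/√N. That sentence ends, and the next begins, "without 95%CI. Categorical secondary outcomes will be compared". The interval for r is therefore excluded by a stated rule, not left out by oversight.

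The primary outcome is "Gastrointestinal Quality of Life Index (GIQLI) - difference between 0 months and 6 months from randomisation". Two secondary outcomes fall under the choice between the rules: "Gastrointestinal Quality of Life Index (GIQLI) at 12 months, 24 months, 48 months and 96 months of randomisation" and "SF-36 quality of life survey score at 6 months, 12 months, 24 months, 48 months and 96 months from randomisation".

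The plan names no test or criterion for normality. It does not require one effect measure for the same questionnaire across visits, and it plans no median difference or Hodges-Lehmann estimate. Under The sample size, the effect is expressed in points: "the study aims to show a difference of 12 GIQLI points", with "the standard deviation being assumed to be 22 points in both groups".

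**The concern.** The main objective is the effect on gastrointestinal quality of life, and GIQLI is collected out to 96 months. At 6 months the reader will see a difference in points with an interval. At any later visit the same instrument may yield a unitless number with no interval, depending on how the observed scores look and on a check that is not defined.

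Two things would be lost at such a visit. The first is the scale: r cannot be set beside the 6-month mean difference or the 12-point difference used for the sample size unless one knows the SD and assumes a distribution. The second is precision: without an interval, a non-significant result does not show whether a relevant effect has been excluded or whether the comparison was simply too small.

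**Working it through.** **Inputs from the documents.** Difference 12 points, SD 22 in both groups and 60 per group (The sample size, which also cites postoperative SDs of 19 to 22). Effect measures are from the analysis plan and visits from Secondary variables. **Assumed:** SDs of 15 and 30 to show a range; normal scores in steps 2 to 4; a left-skewed score with a ceiling of 144 in step 5. The documents give no distributional shape.

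**1. The plan's own figure.** The plan gives no value of r to reproduce. Its 60 per group, used below only as an illustrative size, does not follow from its stated inputs: a two-sided t-test at α = 0.05 with 90% power needs 71.6, so 72 per group, and 60 per group gives 84% power. That is a separate matter, and nothing here depends on it.

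**2. From points to r.** For normal scores with common SD σ and difference δ, P(X > Y) = Φ(δ/(σ√2)). With n per group and N = 2n, the approximate expected value is

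r = (P − 0.5)·n² / √(n²(N + 1)/12) / √N.

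For n = 60 the rank standard deviation is √(3600 × 121/12) = 190.5. At σ = 22: P = Φ(12/31.11) = 0.650; the numerator is 0.1501 × 3600 = 540.5; Z = 540.5/190.5 = 2.84; r = 2.84/√120 = 0.26.

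| SD | P(X > Y) | r for a true 12-point difference | Points implied by r = 0.26 |
|---|---|---|---|
| 15 (assumed) | 0.714 | 0.37 | 8.2 |
| 19 | 0.672 | 0.30 | 10.4 |
| 22 | 0.650 | 0.26 | 12.1 |
| 30 (assumed) | 0.611 | 0.19 | 16.4 |

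The last column inverts the formula: r = 0.26 gives P = 0.6507, and δ = Φ⁻¹(0.6507)·σ√2. The same r corresponds to anything from 8 to 16 points over these SDs.

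**3. Precision that would not be shown.** In 3,000 simulated trials with normal scores, a true difference of 12, SD 22 and 60 per group, 95% of r values lay between 0.09 and 0.42.

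**4. What the 6-month result would show.** The standard error is 22√(2/60) = 4.02. The 95% half-width is 1.98 × 4.02 = 8.0 points.

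**5. A points-scale estimate under skew.** Scores were simulated as 144 minus a gamma variable (shape 2, scaled to SD 22), with a true shift of 12 and 60 per group, in 2,000 runs.

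| Measure | Average estimate | Average 95% limits | Coverage |
|---|---|---|---|
| Hodges-Lehmann shift | 12.0 | 5.4 to 18.6 | 96% |
| Mean difference | 12.1 | 4.2 to 19.9 | 95% |

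With no true difference, the t-test rejected in 4.8% of 10,000 runs. Both measures are valid here and both are in points. The Hodges-Lehmann interval is the narrower: 13.2 points wide against 15.7 or 15.8.

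**6. Exposure.** GIQLI at 12, 24, 48 and 96 months is four comparisons. SF-36 at 6, 12, 24, 48 and 96 months is five, if one score per visit is analysed.

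**The case against.** The strongest reply is that the rule is narrow and the rank test is a sound choice. Most of that stands.

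- **The loss is conditional.** The primary outcome is fixed to a mean difference with interval. Nothing in the documents says later GIQLI or SF-36 scores will be non-normal, so the number of comparisons affected could be zero.
- **r is an effect size.** A reader might infer that r is a p-value in disguise, that results so reported are uninterpretable, or that they cannot be pooled or compared over time. The plan's definition does not support this. Dividing Z by √N removes the sample-size factor, and r conveys direction and a standardised rank effect that can be compared or pooled with other r values. Nor does the plan forbid descriptive medians or means alongside.
- **The rank test has its own merit.** A reader might infer that the Mann-Whitney test serves no purpose because the t-test keeps its type I error under skew. Type I error is only half the matter. With 144 minus gamma (shape 2, scale 16), 60 per group and a 12-point shift, simulated power was about 82% for the t-test and 92% for Mann-Whitney. At 33 per group, roughly the size if the trial stops at the 66-patient interim analysis, it was about 57% and 70%. Replacing the rank method with a mean difference alone could therefore cost precision.
- **The 12-point figure belongs to the sample-size calculation.** No target is stated for later visits, so it serves here as the documents' only benchmark, not as a success criterion at 12 to 96 months.

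None of this restores what the rule removes: an estimate in points and an interval.

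**Conclusion.** The point holds as a reporting weakness for some secondary outcomes. If GIQLI at a later visit, or SF-36 at any visit, is judged non-normal, the planned effect measure has no scale points and no stated precision. It then cannot be compared with the 6-month mean difference, and a null result is uninformative about what has been excluded. At most nine comparisons are exposed (4 + 5), possibly none.

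The text of the plan alone establishes that the interval and the point scale are dropped. The size of the ambiguity in r (8 to 16 points for r = 0.26) rests on normal scores, 60 per group and SDs of 15 to 30, of which only 19 and 22 come from the documents. The results under skew rest on an assumed distribution.

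The documents do not support going further: the primary conclusion is untouched, and the Mann-Whitney test is not itself at fault. The plan should be changed, but the trial's main result does not depend on it.

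**What to change.** Amend the analysis plan in two places.

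1. For GIQLI and SF-36, report the between-group mean difference with 95% CI at every time point, whatever the normality check shows, using a bootstrap or robust interval where scores are skewed. This keeps each instrument on one scale throughout follow-up.
2. Wherever the Mann-Whitney test is used, keep it, and replace or supplement r with the Hodges-Lehmann shift (or the probability of superiority) with its 95% CI.

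The cost is plan wording and slightly more analysis and reporting; no further data or patients are needed. Under marked skew the mean difference may be less precise than the rank-based estimate, which is why the rank test and Hodges-Lehmann interval should stay beside it.

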## 2. Conservative treatment

### Lifestyle guidelines in writing

- Duodecim Medical Publications Information to the patient: The intestinal diverticular disease, 12/11/2012

Pertti Black River ([www.terveysportti.fi](http://www.terveysportti.fi))

- Medical book Duodecim Information for the patient: Constipation 8.10.2012 Pertti Mustajoki

([www.terveysportti.fi](http://www.terveysportti.fi))

Recommendation on the use of fiber supplement.

Action in the event of elective sigmoid resection in a patient randomized to conservative treatment:

Conservative treatment should be tried for at least 6 months of randomisation (= until the first quality of life survey) before it can be concluded that it has failed and the patient referred to elective sigmoid resection. Of course, surgical treatment can be performed earlier if the patient has developed absolute indications for elective sigmoid resection (eg fistula, stricture). If a patient randomized to conservative treatment has to be treated with elective sigmoid resection, the patient should complete the GIQLI and SF-36 quality of life questionnaires at the time of surgery. After surgery, the patient is followed according to the original follow-up schedule (i.e., surveys just before surgery (preoperative visit, etc.), 6 months, 12 months, 24 months, 48 months, and 96 months after the initial randomisation). In accordance with normal research ethical principles, the patient may also opt out of the study altogether, at which point his or her follow-up will cease and he or she will be treated according to normal treatment lines and at the discretion of the attending physician.

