## Schedule, interim analysis and completion of the study

The study is planned to start in summer / autumn 2014. An interim analysis will be performed in the middle of the study, ie for 66 patients. If a statistically significant difference is obtained for the primary outcome already at this stage, the study will not be continued. Otherwise, the study will continue until 133 patients have been randomized. It is estimated that it will take about five years to recruit patients. The follow-up phase will continue for another eight years.

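### Event outcomes followed for up to 96 months are planned only as crude 2x2 comparisons with odds ratios, with no time point, no rule for early end of follow-up and no rule for zero cells

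*Supplement*

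**What the plan says.** The Statistical analysis plan (amendment of 5 August 2020) covers all categorical secondary outcomes in one sentence. They are compared "using Fischer's exact test (if expected cases in one cell <5") or otherwise by the chi-square test, and "effect size will be reported as odds ratios (OR) with 95% CIs". The section closes with "All outcomes will be analyzed using intention-to-treat principle where patients are analyzed in the group where they were randomized to". It names no time-to-event, cumulative-incidence or rate method, and no rule for incomplete follow-up, death or empty cells.

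Under Secondary variables, GIQLI and SF-36 carry explicit assessment times. The event outcomes do not. They include "Recurrence of diverticulitis and Hinchey class", "Undergoing emergency surgery due to diverticulosis / diverticulitis", fistula or stricture, "Mortality (for any reason in both groups") and stoma.

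The Follow-up section gives both arms the same schedule, to 96 months after randomisation, and the Schedule section adds that "The follow-up phase will continue for another eight years". Under Conservative treatment, "the patient may also opt out of the study altogether, at which point his or her follow-up will cease". The sample size section expects about 10% loss, without a horizon or a split by arm. The Hypothesis section names fewer recurrences as one of its two claims.

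**The concern.** A 2x2 table needs each patient classified as having had the event or not. Over a window of up to eight years, some patients will have left event-free before it closes. Counting them as event-free understates risk in the arm with more loss. Dropping them while keeping leavers who had an event overstates risk in that arm. The intention-to-treat sentence settles which arm a patient belongs to, not how an incompletely observed patient is classified. With no time point stated, neither the numerator nor the denominator of the table is defined in advance.

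The comparison is surgery against lifestyle advice, so loss that differs by arm is plausible, though the documents give no figures for it. At stake is the recurrence half of the hypothesis.

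Separately, the odds ratio is a poor sole effect measure for outcomes such as death or stoma, where an arm of about 66 patients may have no events.

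**Working it through.** **Inputs.** The plan states no event rate, no loss by arm and no design figure for event outcomes, so there is no planned figure to reproduce here. Arm size: 133/2 = 66.5, taken as 66. Event risks, and how loss splits between arms, are assumptions shown over a range.

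**1. Early end of follow-up, no true effect.** Let the 8-year risk be *F* in both arms, with constant event rate λ = −ln(1 − *F*)/8. Let loss by year 8 be *d*, independent of the event, with rate γ = −ln(1 − *d*)/8. Then:

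- proportion with an observed event: *a* = λ/(λ + γ) × [1 − exp(−8(λ + γ))]
- proportion followed to year 8 event-free: *s* = exp(−8(λ + γ)) = (1 − *F*)(1 − *d*)
- risk if leavers count as event-free: *a*
- risk if event-free leavers are dropped: *a*/(*a* + *s*)

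Example, *F* = 30%, loss 5% against 15%: λ = 0.0446; γ = 0.0064 and 0.0203; *a* = 0.293 and 0.278.

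- Leavers event-free: (0.293/0.707)/(0.278/0.722) = 1.07.
- Leavers dropped: *s* = 0.665 and 0.595, risks 0.306 and 0.319, odds ratio 0.94.

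| Loss by year 8 | F | OR, leavers event-free | OR, leavers dropped |
|---|---|---|---|
| 10% v 10% | 10%, 30%, 50% | 1.00 | 1.00 |
| 5% v 15% | 10% | 1.06 | 0.94 |
| 5% v 15% | 30% | 1.07 | 0.94 |
| 5% v 15% | 50% | 1.10 | 0.94 |
| 10% v 30% | 10% | 1.14 | 0.88 |
| 10% v 30% | 30% | 1.17 | 0.87 |
| 10% v 30% | 50% | 1.22 | 0.86 |

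The true odds ratio is 1.00 throughout. The direction of the error depends on the classification the plan leaves open. The 5% against 15% rows average the plan's 10%; the 10% against 30% rows average 20% and lie outside it. Under the same independent-loss assumption, a censored time-to-event analysis targets a hazard ratio of 1.00 in every row.

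**2. Zero cells.** The chance of no events in an arm is (1 − *p*)^66:

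- *p* = 1%: 0.99^66 = 0.52
- *p* = 2%: 0.98^66 = 0.26
- *p* = 5%: 0.95^66 = 0.03

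At *p* = 2% in both arms, at least one arm is empty with probability 1 − (1 − 0.264)² = 0.46, and both are empty with probability 0.264² = 0.07.

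What can still be reported, with 66 per arm:

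- **0 v 6 events:** odds ratio 0; exact 95% interval 0 to 0.81; Fisher p = 0.028; Wald interval on the log odds ratio not computable. Adding 0.5 to each cell gives 0.07 (0.004 to 1.27), which disagrees with the exact result about whether 1 is excluded. Risk difference (Newcombe) −9.1 points (−18.4 to −1.8).
- **0 v 0 events:** odds ratio undefined; risk difference 0 (−5.5 to +5.5 points).

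**The case against.** The strongest reply is that the comparison is fair by design. Both arms share one schedule to 96 months, crossover patients keep it, and equal loss leaves the crude odds ratio at 1.00. That stands: a reader might infer that follow-up is unequal by design, and the documents do not support this.

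The Follow-up section also has the local researcher check patient records at each time point, so an unreturned questionnaire need not mean a lost event. This reduces the problem without removing it, because opt-out ends follow-up and the check covers the researcher's own area.

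The bias is modest beside sampling error. At 30% risk and 66 per arm (19.8 expected events each), the standard error of the log odds ratio is √(2/19.8 + 2/46.2) = 0.38, so 95% limits lie a factor of about 2.1 either side. That is fair on size, but not a reason to leave the table undefined.

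A reader might also infer that an empty arm leaves no estimate at all. It does not: Fisher's test, which the plan names for sparse tables, still gives a p-value, and an exact method gives a one-sided bound. The plan does not specify Wald intervals.

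Nor is the elective-resection outcome an odds ratio that cannot be computed. Secondary variables labels it as belonging to the conservative group, so it is naturally descriptive.

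Finally, censored methods assume non-informative censoring and do not cure informative opt-out, and proportional hazards is doubtful with surgery in the first three months and crossover from six. Both cautions stand.

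**Conclusion.** The point holds as a gap in the analysis of secondary event outcomes. The plan fixes a crude 2x2 comparison with an odds ratio, gives these outcomes no time point, and says nothing on early loss, death or zero cells.

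The distortion arises only if loss differs by arm. With leavers counted as event-free it is about 1.06 to 1.10 for a split consistent with the stated 10%, and about 1.14 to 1.22 for a heavier split that the plan does not anticipate. These figures rest on assumed constant rates, independent loss and 8-year risks of 10% to 50%. They are not forecasts, and eight years is used only because it is the longest scheduled follow-up.

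Zero cells are realistic at true risks of 1% to 2% and unlikely at 5%. With one empty arm, what is lost is a finite odds ratio with a Wald interval. The odds ratio is undefined only when both arms are empty.

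The primary outcome is unaffected. The change is worth making because recurrence is part of the hypothesis and the remedy is cheap.

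**What to change.** - **First recurrence, emergency surgery, fistula or stricture:** analyse as time from randomisation, censored at last contact or record review. Show cumulative incidence by arm with death as a competing event, a log-rank test or hazard ratio with 95% confidence interval, and risks at 6, 12, 24, 48 and 96 months. The risks at fixed times do not depend on proportional hazards.
- **Rare or fixed-window binary outcomes, such as mortality and stoma:** state the window and how patients with incomplete follow-up are counted. Report the risk difference with a score-based 95% interval (Newcombe or Miettinen-Nurminen), and an odds ratio only where both arms have events.
- **Elective resection in the conservative arm:** report descriptively.
- **Loss:** report the number and timing of opt-outs, losses and deaths by arm, so that readers can judge the censoring assumption.

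The cost is analysis-plan wording, plus recording an event date at the record review already scheduled. The case report forms are in an appendix not shown, so whether dates are already captured is unknown. The method still assumes that censoring is non-informative.

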## Registration

The study is registered with clinicaltrials.gov before randomization begins.

## Privacy Policy

Personal data of randomized patients are collected in the study folder, and CRF # 1, # 2, and # 3 are completed for them. Patients who meet the inclusion criteria and thus are evaluated for participation in the study will be accounted for, how many patients will be excluded from the study, and for what reason (fulfillment of the exclusion criterion, refusal, etc.). Personal data of patients who dropped out of the study will not be collected. The material to be collected is stored in a locked state and the electronic data is protected by passwords and encryption on computers.

## **Background**

Diverticulosis is an increasingly common ailment in the aging population. An estimated 25% develop acute diverticulitis (Biondo et al., 2012). The prognosis of acute diverticulitis is related to its severity measured according to the Hinchey classification. The mildest diverticulitis heals on its own, while mortality from diverticulitis that causes fecal peritonitis is high (Wasvary et al., 1999). Peritoneal inflammation caused by diverticulitis usually leads to an emergency sigmoid resection and possible intestinal contents diversion through the stoma. In contrast, milder forms of acute diverticulitis are usually treated conservatively with intravenous antibiotics and abscesses are drained.

It has previously been recommended that patients with recurrent diverticulitis undergo elective sigmoid resection to avoid further problems with complicated diverticulitis (Rafferty et al., 2006). However, retrospective work has found that the most difficult diverticulitis episode is usually the very first one, and the occurrence of complicated diverticulitis decreases with the recurrence of diverticulitis (Chapman et al., 2006; Ritz et al., 2011). Second, elective surgery for complicated diverticulitis (e.g., abscess) has been recommended (Rafferty et al., 2006). However, this recommendation has also recently been questioned (Gaertner et al., 2013). On the other hand, elective sigmoid resection has been shown to improve quality of life in selected patients with either recurrent diverticulitis or complicated diverticulitis (Forgione et al., 2009; Pasternak et al., 2011).

Current knowledge of who should have elective sigmoid resection is very limited, is based on retrospective comparative series or prospective studies that lack a control group. To date, no randomized, prospective study comparing surgical treatment to conservative treatment in patients with a relative indication (recurrent diverticulitis, complicated diverticulitis, pain after acute diverticulitis) to elective sigmoid resection has been published. An extensive recent treatment recommendation for diverticulitis cannot provide definitive recommendations for the selection of patients for elective sigmoid resection due to the lack of randomized work (Andersen et al., 2012).

The main objective of the study is to investigate the effect of elective sigmoid resection on gastrointestinal quality of life by comparing surgical treatment to conservative treatment in a randomized prospective multicenter study. The secondary objective is to investigate recurrence, mortality, and surgical complications of diverticulitis.

